### Study design

This is a prospective, comparative, and single-blind N-of-1 trial, which includes 3 crossover comparisons. Each comparison includes an 8-week treatment period (A) and an 8-week control period (B). According to the random number generated by Strategic Applications Software (SAS), the random arrangement of AB or BA is presented in each cycle (Fig. 1).

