### Statistical analysis

Statistical analysis will be performed by Statistical Package for the Social Sciences (SPSS) for version 25.0. Descriptive statistics will be used to analyze demographic characteristics of participants, including age and gender. Continuous variables will be presented as mean ± standard deviation. The primary and secondary outcomes will be analyzed using the full analysis set. Each patient’s paired trial is treated as an independent trial. For the in-group effects, the paired *t*-test is used for the data with normal distribution, and the Wilcoxon rank sum test is used for the data with non-normal distribution. For the intergroup effect, three pairs of data with normal distribution will be used with repeatability measure ANOVA test, and linear mixed-effects model will be used with non-normal distribution. For missing values, we will use a mixed-effects model for repeated measures. The *P* (2-tailed) value with threshold less than 0.05 will be considered statistically significant.

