Generally speaking, N-of-1 trial is a double-blind, randomized, multi-crossover trial with a single case as a control to evaluate the efficacy of the two therapies. N-of-1 trial belongs to RCT. In clinical practice, clinicians and patients pay more attention to the changes of curative effect after individuals taking medicine. This leads to RCT-based population evidence that may not be appropriate for individualized patients. Therefore, the research method for individual patient’s curative effect evaluation is indispensable. That is why N-of-1 came into being.

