The clinical research is the first application in RP patients with the TpES therapy. With respect to the rationale for carrying out N-of-1 trial rather than RCT, we take the following reasons into consideration.N-of-1 trials are randomized, prospective, controlled, multiple crossover trials in a single patient. Such trials are suitable for the following clinical applications: (1) chronic disease; (2) experimental treatments for rare diseases or with little or no previous research; (3) doubtful about the efficacy and safety of interventions for certain diseases; (4) the intervention has the characteristics of quick onset and short half-life period and the effect can disappear quickly after the intervention is stopped.RP comprises a group of inherited retinal degenerative diseases with a prevalence of 1 in 4000, affecting 2 million persons globally. RP is associated with 3000 mutations in 100 genes. As a rare and chronic disease, adequate recruitment for group trials is not always feasible, informed consent is difficult to obtain, and retention is difficult too. Compared with RCT, the N-of-1 trial has higher power and requires smaller sample sizes.RP is a highly heterogeneous disease. Studies have shown that genotype plays an important role in RP progression. Besides it, there are many other risk factors that may have effect on the progression of RP, such as inheritance patterns, smoking, physical activity, and other demographic and environmental factors. Due to the small cohort sample size and the large clinical heterogeneity of RP patients, it is difficult to obtain high-quality evidence of therapeutic effectiveness. With the consideration of heterogeneity, N-of-1 trial is a more suitable choice.There have been no reports of transpalpebral electrical stimulation for RP treatment up to now. It is an individualized treatment, and the intensity of stimulating current varies with the condition of the retinopathy in each patient. In the trial, patients will perform the treatment by themselves. Therefore, N-of-1 trial has better feasibility than conventional RCT. Moreover, the intervention has the characteristics of quick onset, and the effect can disappear relatively quickly after the intervention is stopped, which make it suitable for N-of-1 trial.

Taken together, based on the characteristics of RP and the intervention method, it is very suitable for the study of RP.

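### Treating each paired trial as independent and testing undefined 'in-group' effects at 0.05 serves neither reading: three pairs per patient are too few, and pooled pairs ignore clustering

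*Protocol article*

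**What the plan says.** The Study design section describes an N-of-1 trial "which includes 3 crossover comparisons", each made of one 8-week treatment period and one 8-week control period in random order. Each patient therefore contributes three treatment-control pairs, and 12 patients contribute 36.

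The Statistical analysis section sets the unit: each patient's "paired trial is treated as an independent trial". It continues: "For the in-group effects, the paired *t*-test is used for the data with normal distribution", while the "Wilcoxon rank sum test is used for the data with non-normal distribution". The intergroup effect is to be analysed by repeated-measures ANOVA on the three pairs if the data are normal, and by a linear mixed-effects model if they are not. The threshold is two-sided 0.05. Neither 'in-group' nor 'intergroup' is defined.

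The Discussion gives several reasons for the design. One is that, for individual patients, "curative effect evaluation is indispensable". Another is the variability of the disease: "With the consideration of heterogeneity, N-of-1 trial is a more suitable choice". Rarity, feasibility, smaller sample size and quick onset and offset are also given.

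**The concern.** The sentence on independence can be read in two ways. Each patient may be a separate small trial, analysed on three pairs. Or each treatment-control pair may be a separate trial, with all pairs pooled across patients. The article does not say which.

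On the first reading, the named tests have almost no ability to detect an effect in a patient, and a patient who benefits could be labelled a non-responder. On the second, pairs from the same patient are counted as unrelated. That understates the standard error if the effect differs between patients, which the heterogeneity argument makes plausible.

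Two further choices add to the problem. The rank sum test is for unpaired samples, yet the data are paired. And the choice between ANOVA and a mixed model turns on normality, so with normal data the one named method that could readily carry a between-patient variance of effect is not used for the treatment comparison.

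**Working it through.** **Inputs.** Three pairs per patient (Study design). Difference 1.43, SD 1.93, 80% power, two-sided 5%, 10 patients raised to 12 (Sample size). The quoted group means give 2.06 − 0.73 = 1.33, so both differences are carried. The SD of a within-patient difference is not given. I assume 1.93, or 1.93 × √2 = 2.73 if the two period values are uncorrelated.

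**1. The plan's own figure.** Two-sample formula: 2 × (1.960 + 0.842)² × 1.93² / 1.43² = 28.6 observations per period. Spread over three cycles, 28.6 / 3 = 9.5, rounded up to 10, which matches. One pair per patient does not match: (1.960 + 0.842)² × 1.93² / 1.43² = 14.3, so 15. The article does not state its formula, so the division by three is an inference. It suggests that the trial was sized for pairs pooled over patients.

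**2. Within a patient, exact Wilcoxon tests.**
- Rank sum, 3 v 3: smallest two-sided P = 2 / C(6,3) = 2/20 = 0.10.
- Signed rank, 3 pairs: smallest two-sided P = 2 / 2³ = 0.25.

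**3. Within a patient, paired t-test.** With 2 degrees of freedom the critical |t| is 4.303, so the mean difference must exceed 4.303/√3 = 2.48 SDs. Noncentral-t power:

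| SD of differences | difference 1.33 | difference 1.43 |
|---|---|---|
| 2.73 | 8.2% | 8.7% |
| 1.93 | 11.4% | 12.3% |
| 1.0 (assumed) | 26.7% | 29.6% |

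The 95% interval for one patient has half-width 4.303 × SD/√3, that is ±6.8 at SD 2.73 and ±4.8 at SD 1.93, against a planned effect of about 1.4.

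**4. Pairs pooled as independent.** Let σ be the SD of differences within a patient and τ the between-patient SD of the effect. With three pairs per patient, the variance of the pooled mean is understated by a factor of about 1 + 2ρ, where ρ = τ²/(τ² + σ²). Type I error is then about 2Φ(−1.96/√(1 + 2ρ)).
- σ = 2.73, τ = 0.5: ρ = 0.032, factor 1.065, about 5.8%.
- σ = 1.93, τ = 1.5: ρ = 0.377, factor 1.753, about 13.9%.

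Simulation of the 36-pair t-test with mean effect zero gave 5.8%, 7.8% and 10.6% at σ = 2.73, and 6.5%, 10.0% and 14.0% at σ = 1.93, for τ = 0.5, 1.0 and 1.5. A t-test on the 12 patient means stayed at about 5% throughout.

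**5. What a mixed model could deliver.** At σ = 2.73 the error SD of a patient's mean difference is 2.73/√3 = 1.58. The standard error of a shrunken individual estimate, including that of the mean, is 0.64, 0.93 and 1.14 for τ = 0.5, 1.0 and 1.5, treating τ as known. But τ must be estimated. The moment estimate of its variance is zero or negative with probability 0.45, 0.28 and 0.13 at those values, and all shrunken estimates then coincide.

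**The case against.** The strongest reply is that the article nowhere says the in-group tests are run within a patient. The stated objective is overall efficacy and safety, the sample size is for a mean difference, and its figure reproduces on pooled pairs. If pooling is meant, the three-pair limits do not apply. This stands, and it is why the point is put conditionally. Pooling as independent brings its own error, however.

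A second reply is that a condensed article may leave individual estimates and random-effects structure to the full protocol or analysis plan. This also stands: a reader might infer that no individual or heterogeneity estimate is planned, but the documents support only that none is stated here. The unit, the tests and the threshold, by contrast, are stated.

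Third, the intergroup analysis may be the decisive one and may respect the patient level. That is possible, but the article does not say which analysis decides.

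Other tempting readings go too far:
- *Every patient will almost surely be non-significant.* At 8.2 to 12.3% power per patient, the chance that all 12 t-tests miss is 0.918¹² = 0.36 to 0.877¹² = 0.21 (independent patients, common effect). At least one significant result is likelier than not.
- *The rank sum test can never reach 0.05.* This holds for exact P values. The uncorrected normal approximation gives 0.0495 at complete 3 v 3 separation, though with three values per period it should not be relied on.
- *Individual evaluation is the sole justification, or heterogeneity is the reason for three cycles.* It is one reason among several, and the number of cycles is not tied to it.

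**Conclusion.** The point holds in conditional form: the stated unit and tests work poorly on either reading. Within a patient, significance at 0.05 is impossible with exact Wilcoxon tests and has 8 to 12% probability with the t-test at the protocol's figures, rising to about 30% if the SD of differences were 1.0. Pooled as independent, the nominal 5% becomes about 6 to 14%.

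The first range rests on a within-patient SD inferred from a group study's 1.93. The second rests on an assumed τ of 0.5 to 1.5; with τ = 0 there is no inflation. Confidence is moderate because the intended reading is unknown. The analysis text should be changed, but the design itself is not invalidated.

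**What to change.** Define the unit of analysis. Replace the independent-pair tests and the normality-dependent choice by one linear mixed model on all period values, with a random participant intercept and a random participant-by-treatment effect, used whatever a normality test shows. Make the mean treatment effect the main inference, with degrees of freedom that reflect 12 patients. Draw no conclusion about an individual from P < 0.05. Report the between-patient SD of the effect, and each participant's shrunken estimate with its 95% interval, as descriptive results.

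The cost is analysis wording: no new data or visits, and the plan already names a linear mixed-effects model. The downside is that with 12 patients the heterogeneity SD will be imprecise and may be estimated as zero. The report must say so, and must not read a zero as evidence that all patients respond alike.

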### Sample size

The sample size was calculated from SUN’s previous study [16]. The primary outcome was the change of mean defect (MD) value of VF after 8 weeks of treatment compared with baseline. Based on the reference (Sun et al.), the MD value of the treatment group is 2.06 ± 1.73. The MD value of the control group is 0.73 ± 1.93. The difference between the effect values of the treatment period and the control period was 1.43, and the standard deviation of the two periods was 1.93. When a two-tailed test with a test power of 80% and significance level of 5% was applied to the research, 10 cases were calculated [17]. Taking into account of 20% dropout rate, we ultimately identified 12 participants.

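### The non-normal fallback for the paired t-test is an independent-samples test, and non-normality is the wrong trigger for moving from repeated-measures ANOVA to a linear mixed model

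*Protocol article*

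**What the plan says.** All the relevant rules are in the Statistical analysis section of the protocol article.

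- **In-group effects:** a paired t-test if the data are normal; if not, "the Wilcoxon rank sum test is used for the data with non-normal distribution". The term in-group is not defined.
- **Intergroup effect:** if normal, "three pairs of data with normal distribution will be used with repeatability measure ANOVA test"; if not, a "linear mixed-effects model will be used with non-normal distribution".
- **Missing data:** "For missing values, we will use a mixed-effects model for repeated measures".
- **Unit of analysis:** each patient's "paired trial is treated as an independent trial".

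Under Study design, each of the three comparisons holds one treatment and one control period in the same patient, so the data are paired throughout. The Sample size section is built on change in MD from baseline after 8 weeks and arrives at 10, then 12, participants. No other section alters these rules.

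**The concern.** The same sentence treats the in-group data as paired when they are normal and as two unrelated samples when they are not. The paired counterpart of the t-test is the Wilcoxon signed-rank test. The rank-sum test leaves the differences between patients in the error term, and removing those differences is a main reason for an N-of-1 crossover. The Discussion itself justifies the design by the heterogeneity of the disease.

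The intergroup rule has a different fault. A linear mixed model assumes normal random effects and residuals, so it does not cure the non-normality that is supposed to call for it. What the rule does do is leave two candidate primary methods, chosen after looking at the data from 12 patients.

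**Working it through.** **Inputs from the Sample size section.** Change in MD 2.06 ± 1.73 (treatment) and 0.73 ± 1.93 (control); stated difference 1.43; SD 1.93; two-sided 5%; power 80%; 20% dropout. The stated means give 2.06 − 0.73 = 1.33, so both differences are used below and labelled. Within-pair correlation ρ and between-patient SD are not given; they are assumed over a range.

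**The plan's own figure.** Two-sample formula: n = 2 × (1.96 + 0.84)² × 1.93² / 1.43² = 28.6, so 29 per condition. Then 29 / 3 cycles = 9.67, so 10, and 10 × 1.2 = 12. Dividing by three cycles is an inference, because the protocol does not state its formula. It fits the statement that each pair counts as independent, which gives 30 pairs (10 patients) or 36 (12 patients).

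**Level of the rank-sum test on paired data.** The test takes the variance of the difference as if ρ were 0, whereas the true variance is smaller by a factor of about 1 − ρ. Its null rejection rate is therefore roughly 2 × [1 − Φ(1.96 / √(1 − ρ))]:
- ρ = 0.5: 1.96 / √0.5 = 2.77, giving about 0.6%.
- ρ = 0.8: 1.96 / √0.2 = 4.38, giving about 0.001%.

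Simulation (4,000 trials per setting, normal data) gives 0.8% at ρ = 0.5 with both 12 and 36 pairs, and 0.05% or less at ρ = 0.8. The signed-rank test stays between 4% and 6%.

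**Power, reading 1: SD 1.93 in each period, pairs taken as independent in the test.**

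| Setting | ρ | Signed-rank | Rank-sum |
|---|---|---|---|
| 30 pairs, difference 1.43 | 0 | 0.77 | 0.78 |
| | 0.5 | 0.98 | 0.86 |
| | 0.9 | 1.00 | 0.97 |
| 36 pairs, difference 1.33 | 0 | 0.80 | 0.81 |
| | 0.5 | 0.98 | 0.87 |
| | 0.8 | 1.00 | 0.96 |
| | 0.9 | 1.00 | 0.99 |

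The largest gap is about 12 percentage points.

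**Power, reading 2: SD 1.93 is that of the paired difference** (assumed), so the per-period SD is 1.93 / √(2(1 − ρ)): 1.93 at ρ = 0.5, 3.05 at 0.8 and 4.32 at 0.9. With 12 pairs and difference 1.33, signed-rank power is about 0.54 throughout. Rank-sum power is 0.60, 0.30, 0.05 and 0.006 at ρ = 0, 0.5, 0.8 and 0.9.

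**Power, reading 3: raw MD before and after treatment,** change 2.06 ± 1.73, with between-patient SD assumed.

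| Between-patient SD (dB) | 10 pairs: signed-rank | 10 pairs: rank-sum | 30 pairs: signed-rank | 30 pairs: rank-sum |
|---|---|---|---|---|
| 0 | 0.92 | 0.95 | 1.00 | 1.00 |
| 1.73 | 0.90 | 0.50 | 1.00 | 0.99 |
| 3 | 0.91 | 0.14 | 1.00 | 0.86 |
| 5 | 0.90 | 0.01 | 1.00 | 0.36 |

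**Mixed-model branch.** With 30 pairs and a random patient intercept, simulated type I error was 0.038 to 0.053 and power 0.95 to 0.98 under normal, t (3 df) and lognormal errors. The model itself does no damage here.

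**The case against.** Several points on the other side have force.

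- **It may be a slip.** The name follows the paired t-test in the same sentence, so signed-rank may have been meant. As written, though, an analyst would run the wrong test.
- **It may not touch the treatment effect.** The rank-sum test is named only for the undefined in-group effects. If intergroup means treatment versus control, the rank-sum test never tests the treatment contrast, and readings 1 and 2 then do not apply.
- **The error is conservative.** Null rejection falls below 5%, so it adds no false positives.

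Three stronger readings are tempting, and the document does not support them. A reader might infer that the planned test loses most of its power. That needs a high correlation together with few pairs or a large between-patient spread. The sizing inputs do not imply this: the figures of 5% and below under reading 2 require per-period SDs of 3.05 or more, against the stated 1.73 and 1.93. The heterogeneity described in the Discussion is not an SD of MD.

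A reader might also infer that the ANOVA branch discards every patient with a missing period, which at 20% dropout is 2 to 3 of 12. The section already promises a mixed model for missing values, so what remains is unclear wording about which model applies when.

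Finally, tests within one patient (three pairs) cannot reach 0.05, but this is no argument for the signed-rank test. The smallest two-sided p is 2/20 = 0.10 for rank-sum and 2/8 = 0.25 for signed-rank.

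**Conclusion.** Both rules are wrong as written, in different ways.

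The rank-sum test is the wrong test for paired data and falls well short of its nominal level: about 1% at ρ = 0.5 and near 0% at ρ = 0.8, assuming normal data. Its power cost is conditional. There is none at ρ = 0, and at most about 12 points with 30 to 36 pairs taken as independent and SD 1.93 per period. It becomes large only with few pairs or a wide between-patient spread, as raw before-and-after MD could have. The document gives neither quantity, so no single figure can be attached.

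The linear mixed model is not a wrong method for these data. Only its trigger is wrong, and the consequence is that the primary intergroup method is left to a normality check in 12 patients.

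**What to change.** 1. Replace the rank-sum test by the Wilcoxon signed-rank test wherever the data are paired, and say what in-group compares.
2. Make a linear mixed model on all available periods the single primary intergroup analysis, whatever a normality check shows. This agrees with the mixed model already promised for missing values.
3. Drop the repeated-measures ANOVA branch.
4. As the robustness check, use a signed-rank test on the patient-mean treatment-minus-control differences, one value per patient. With 12 patients its smallest two-sided p is 2/2¹² = 0.0005, so 0.05 can be reached.

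The cost is analysis wording only, with no extra patients, visits or measurements. The sponsor gives up the freedom to choose the method after seeing the distribution.

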### Quality supervision

#### Management of study participants

We have prepared a reasonable recruitment plan for the convenience of research assistants and participants. For the communication with the study participants, we record participants’ WeChat account and mobile phone number. Especially in the control period, we communicate with participants regularly, know about their mental state and illness, and obtain maximum cooperation from participants. In addition, if any harm is associated with this clinical trial, compensation will be provided for the damage associated with the trial.

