#### Study period of control (no TpES intervention)

A TpES device is applied to the eyelids, but no electrical stimulation is given, and no pulsation is felt. Everything else remains the same.

During treatment and control periods, other treatments for RP will be discontinued, such as complementary therapies (herbal remedies and acupuncture) or other medications, throughout the study. Participants can take Western medicine to treat systemic diseases, such as hypertension or hyperlipidemia. Medication use will be recorded in detail in the case report form (CRF).

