#### Randomization and blinding

Allocation of cases to study groups is undertaken by a person not participating in the trial with the help of the generation of random sequencing using the SAS statistical software. Allocations are placed in sealed envelopes. Participants will be allocated an individual trial identification number. Research assistants will perform the allocation of patients to the study groups by opening of sealed envelopes at the time and prior to the first intervention cycle.

Due to the nature of the intervention, only the principal investigator is blinded to the treatment in this study. Unblinding is permissible only if the intervention is considered necessary to guide clinical management and with the consent of the principal investigator.

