#### Primary outcome

In this study, the primary outcome is VF [18]. Quantitative index of VF, including MD, mean sensitivity (MS), and square root of loss variance (sLV), will be examined by OCTOPUS automatic perimetry. The 32-test procedure is suitable for visual acuity greater than 0.3, and the LVC test procedure is suitable for visual acuity less than 0.3. The examination time points are before treatment and then at week 8, week 16, week 24, week 32, week 40, and week 48 (Table 1).

**Table 1 Tab1:** Schedule of enrolment, intervention, assessment

Item	Screening	Observation period						
		Cycle 1		Cycle 2		Cycle 3		Closeout
Time point	Enrollment	Weeks 1–8	Weeks 9–16	Weeks 17–24	Weeks 25–32	Weeks 33–40	Weeks 41–48	
Demographic data	√							
Medical history	√							
Informed consent form	√							
BCVA	√	√	√	√	√	√	√	
VF	√	√	√	√	√	√	√	
OCT	√	√	√	√	√	√	√	
FAF	√	√	√	√	√	√	√	
ERG	√	√	√	√	√	√	√	
NEI VFQ-25	√	√	√	√	√	√	√	
Adverse event		√	√	√	√	√	√	

√ Items that must be performed

*BCVA* Best corrected visual acuity, *VF* Visual field, *OCT* Optical coherence tomography, *FAF* Fundus autofluorescence, *ERG* Electroretinogram, *NEI VFQ-25* 25-Item National Eye Institute Visual Function questionnaire

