#### Secondary outcomes

Secondary outcomes include BCVA, optical coherence tomography (OCT), fundus autofluorescence (FAF), electroretinogram (ERG) and vision-related quality of life (VRQoL). The examination time points are before treatment and then at week 8, week 16, week 24, week 32, week 40, and week 48. BCVA will be examined by ETDRS visual acuity chart [19]. ERG includes five indexes, rod response, maximal combined rod-cone response, scotopic oscillatory potentials, cone response, and photopic 30 Hz flicker [20]. OCT measures the thickness of macular fovea [21]. Heidelberg ultra-wide angle photography technique will be used to examine the fundus images under the natural pupil [19]. The VRQoL is evaluated with NEI VFQ-25 questionnaire [22]. The NEI VFQ-25 consists of 26 items that address 12 aspects of daily living as follows: general health, general vision, near vision, distance vision, driving, peripheral vision, color vision, ocular pain, role limitation, dependency, social function, and mental health. Under the guidance of a research assistant, the questionnaire is self-administered by the study participants themselves.

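### Participant contact is planned to be heavier in the control period, so it varies with treatment in the A–B comparison and can bias it; contact should be the same in both periods

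*Protocol article*

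**What the plan says.** Under Management of study participants, in the Quality supervision part of the protocol article, the contact plan reads: "Especially in the control period, we communicate with participants regularly, know about their mental state and illness, and obtain maximum cooperation from participants". No similar emphasis is given for the treatment period.

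The control period is described under Study period of control: "A TpES device is applied to the eyelids, but no electrical stimulation is given, and no pulsation is felt". The next sentence is "Everything else remains the same".

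Under Randomization and blinding, "only the principal investigator is blinded to the treatment in this study". The same section says: "Research assistants will perform the allocation of patients to the study groups by opening of sealed envelopes".

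The efficacy contrast is A versus B within participant, over three cycles (Study design). Visual field is the primary outcome, and its indices "will be examined by OCTOPUS automatic perimetry". Among the secondary outcomes, "BCVA will be examined by ETDRS visual acuity chart", and the NEI VFQ-25 is completed by the participant with guidance from a research assistant. Safety evaluation provides for an examination at the start and end of every period and for reports after daily sessions. Table 1 marks adverse events in all six periods.

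**The concern.** A crossover comparison attributes the A–B difference to the treatment because, on average, nothing else differs between A and B. Here the plan states that something else does differ: staff attention, enquiry about mental state and health, and effort to secure cooperation are all stressed in B.

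The affected outcomes are those that depend on how the participant feels, tries or reports. The NEI VFQ-25 is the most exposed, because its domains include mental health, role limitation and social function, and mental state is a named topic of the extra contact. Automated perimetry and ETDRS acuity depend on attention and effort, so they may be affected too. Health enquiry between visits can also bring out incidental adverse-event reports, and more of it in one period type would make that part of ascertainment unequal. OCT and FAF, and largely ERG, are much less exposed.

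**Working it through.** The document gives no number for contacts in either period, so there is no stated figure to reproduce. The check sets the sections side by side and asks whether the design would remove a contact effect.

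**1. Does contact differ by period type?** The contact sentence singles out the control period. The wording implies some contact in A as well, so the difference is one of degree, but the emphasis means nothing unless B receives more.

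**2. Can staff and participants tell the periods apart?** Yes. Research assistants open the envelopes. In A, participants turn a knob until a flash sensation just appears (Study period of treatment); in B they feel nothing. Blinding the principal investigator does not prevent contact from following the period.

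**3. Does randomising the order remove the effect?** Write τ for the treatment effect, π for the change from the first to the second period of a cycle, c_A and c_B for contact intensity, and β for the effect of one unit of contact on the outcome. The expected A minus B difference in a cycle is:

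- order AB: τ + β(c_A − c_B) − π
- order BA: τ + β(c_A − c_B) + π

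With both orders equally frequent, the mean is τ + β(c_A − c_B). The time term cancels and the contact term does not. Averaging three cycles reduces random error but leaves β(c_A − c_B) unchanged. The term vanishes if c_A = c_B, or if contact has no effect on that outcome (β = 0).

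**4. Does the described analysis address it?** The paired tests, repeated-measures ANOVA and mixed model under Statistical analysis compare the periods as delivered. None of them, as described, separates contact from stimulation.

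**5. Scale, by assumption only.** Neither β nor c_A − c_B is in the document. Sample size states a planned difference in mean defect of 1.43. Suppose, purely as an assumption, that extra contact moved the control-period value favourably by 0.1 to 0.5:

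- 0.1: 1.43 − 0.1 = 1.33, and 0.1/1.43 = 7%
- 0.2: 1.43 − 0.2 = 1.23, and 0.2/1.43 = 14%
- 0.3: 1.43 − 0.3 = 1.13, and 0.3/1.43 = 21%
- 0.5: 1.43 − 0.5 = 0.93, and 0.5/1.43 = 35%

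A shift in the other direction would enlarge the difference by the same amounts. These figures show only how a shift would carry through to the estimate. Nothing in the document says that a shift of any such size would occur.

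**The case against.** The strongest reply is that this is one loosely worded sentence in a retention paragraph. Keeping unblinded participants engaged while they receive no current is a legitimate aim, and a detailed contact schedule is something an article may leave to the full protocol. That is fair, and the absence of a schedule is not the point here. The point is what the article does state, which is an emphasis on one period type. The retention aim would be served equally well by the same contact in both.

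Several stronger readings are tempting, and the document does not support them.

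- **A flat self-contradiction.** A reader might set "Everything else remains the same" against the contact plan and call them incompatible. That sentence directly follows the description of the device without current, so it most naturally covers the device procedure. There is tension with the evident intent, but not a clear contradiction.
- **Adverse-event counts raised in B, making TpES look safer.** Scheduled collection is the same in both periods (Safety evaluation, Table 1), and the contact sentence does not say that messages collect adverse events. Scaling event counts by an assumed contact ratio would ignore those common channels. Only incidental reporting remains in question.
- **Bias toward the null.** More support in B could raise scores there, but the document gives no basis for fixing the sign.
- **Contact fully confounded with treatment.** If contact differs only in degree and is logged, a sensitivity analysis is at least possible.

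It also stands that perimetry is automated and done at the same 8-week points in both periods, that patients judged unable to give reliable fields are excluded, and that the examining departments work to a standard procedure. These limit the exposure of the primary outcome. Participants' knowledge of their allocation is a separate problem, and for the questionnaire it may well be a larger one.

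**Conclusion.** The concern holds as a stated difference in co-intervention. Contact is planned to be heavier in B than in A, it follows period type, and neither the randomised order nor the three cycles balance it. The main exposure is the NEI VFQ-25; an effect on perimetry and BCVA is possible, and incidental adverse-event reporting may become unequal. No size or direction can be given from the document.

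The conclusion rests on two assumptions: that the emphasis in the contact sentence will be carried out in practice, and that contact has some effect on outcomes that depend on report or effort. If either fails, the bias is nil. This is an avoidable weakness that is cheap to remove. It is not a flaw that invalidates the trial.

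**What to change.** In Management of study participants, delete the opening qualifier that singles out the control period. State instead that the frequency, timing and content of contact, including any enquiry about health or mental state, are the same in treatment and control periods, and that every contact is logged in the CRF. A single short script used in both periods would achieve this. The log would show whether contact was in fact equal and would permit a sensitivity analysis if it was not.

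The change takes a sentence or two. The downside is a few more messages in treatment periods or slightly fewer in control periods. Sample size, visits, device procedure and clinical management are unaffected.
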